### Outcome measures

The outcome measures will be measured by questionnaires at baseline and six-months after baseline. Baseline is defined as the start of the intervention, just before the first contact between the ergonomics consultant and the research coordinator in the company.

#### Primary

The use of ergonomic measures is the primary outcome measure and is defined as whether ergonomic measures are used during the last two months by the individual construction workers. The ergonomic measures are defined in four clusters: 1) mechanical measures for horizontal or vertical transportation, such as a crane, 2) ergonomic measures for raising equipment or materials, such as a raised mortar hod, 3) ergonomic measures to adjust working height on the worksite, and 4) ergonomic handtools. Construction workers will be asked at baseline and after six months whether they used ergonomic measures during the last two months during their work (yes or no). Examples of the ergonomic measures are adjusted for the different occupations.

In addition, construction workers are asked at the end of the intervention how many days they could and did use the implemented ergonomic measure during the previous 10 working days.

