### Interventions

The intervention is based on the PE intervention used by van der Molen *et al*. [12] but has been adapted with respect to the guidance strategies. The original PE intervention consisted of a six-step approach in which different company stakeholders (i.e., the CEO, the prevention worker, work planners, foremen, and construction workers (i.e., blue-collar workers)) participated. In the intervention of this study, two ergonomics consultants make, based on the original six-step approach, two protocols of the PE intervention, one for the face-to-face guidance strategy, in which the intervention is guided through one telephone contact and four personal contacts of the ergonomics consultant, and one for the e-guidance strategy, in which the intervention is guided with the help of 13 email contacts. An overview of both guidance strategies is given in Figure 1. During the intervention, costs concerning the guidance by the ergonomics consultants is paid out of research budget. Construction companies are free to choose which ergonomic measure they wish to implement. The maximum duration of each guidance strategy is six months.

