### Sample size

The sample size is based on detecting a difference in the use of a new ergonomic measure between the face-to-face guidance strategy and the e-guidance strategy. In a study of Jensen and Friche [6], it was found that daily use of new introduced construction working methods could be at least 10%. We have decided that a 15% absolute difference in use of newly introduced ergonomic measures between the two guidance strategies is a realistic and relevant difference.

Based on a power calculation using the Nquery Advisor software [25], 113 workers per group must be included for a difference of 15% (from 10% to 25%) with an alpha of 0.05 (two-tailed) and a power of (1-beta) = 0.80. A small cluster effect on the use of ergonomic measures at the level of the construction companies will be anticipated (ICC = 0.01). The construction companies have influence on the use of ergonomic measure by their employees, therefore there is a correlation between company and its employees. Since there is no interaction between the participating companies and because of the different characteristics of the companies (e.g. culture within the company, different trades) the assumption is that the correlation between the companies will be small. Based on the inclusion criteria, the assumption is made that the average number of construction workers (n) within a construction company is on average 25. This results in a cluster effect of 1.24 (1 + ((n-1) × ICC) and an adjusted sample size of 140 per group. To reach this sample size, we must include six construction companies per group.

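### The sample size is calculated for use of a newly introduced ergonomic measure, but the primary outcome is any use of any ergonomic measure in two months, so the stated 80% power does not apply to it

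*Protocol article*

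**What the plan says.** All references are to the protocol article.

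- **Outcome measures, Primary.** The outcome is "defined as whether ergonomic measures are used during the last two months by the individual construction workers". At baseline and at six months workers are asked "whether they used ergonomic measures during the last two months during their work (yes or no"). Four clusters count, from "mechanical measures for horizontal or vertical transportation, such as a crane" to hand tools. Nothing limits the item to the measure that the company selects and introduces.
- **Same section, additional item.** At the end of the intervention only, workers are also asked "how many days they could and did use the implemented ergonomic measure during the previous 10 working days". This item reappears in the Economic evaluation.
- **Sample size.** "The sample size is based on detecting a difference in the use of a new ergonomic measure" is how the section opens. The cited source is said to show that "daily use of new introduced construction working methods could be at least 10" per cent, and the target is "a 15% absolute difference in use of newly introduced ergonomic measures between the two guidance strategies". The resulting figures are 113 workers per group for 10% vs 25% (two-sided alpha 0.05, power 0.80), a design effect of 1.24 from an ICC of 0.01 and 25 workers per company, 140 per group, and six companies per group.

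**The concern.** The planning variable and the primary outcome differ in what they count: a newly introduced measure in one, any measure in the other. The source of the 10% also differs in frequency, since it concerns daily use whereas the outcome scores any use in two months. No sentence connects the 10% to the primary item.

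Two things are at stake. First, the power of a comparison of proportions depends on the base rate, so 80% at 10% vs 25% says nothing definite about an outcome with another base rate. Second, a worker who already uses some measure answers yes whether or not the new one is taken up. A real 15-point difference in new uptake can therefore appear as a smaller difference on the primary item.

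**Working it through.** **1. Reproducing the plan's figure.** Inputs from Sample size: p₁ = 0.10, p₂ = 0.25, d = 0.15, two-sided alpha 0.05, power 0.80. With p̄ = (p₁ + p₂)/2:

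m = [1.96·√(2p̄(1−p̄)) + 0.8416·√(p₁(1−p₁) + p₂(1−p₂))]² / d² = [1.96·√0.28875 + 0.8416·√0.2775]² / 0.0225 = 99.5

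With continuity correction: n = (m/4)·[1 + √(1 + 4/(m·d))]² = 112.5, rounded up to **113**, as stated. Design effect: 1 + 24 × 0.01 = 1.24. Then 113 × 1.24 = 140.1 (stated 140), and 140/25 = 5.6, so six companies. The arithmetic is sound for the variable it describes.

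**2. The same method at other base rates.** The protocol gives no rate for two-month any use, so the base rate is an assumption, shown over a range with the 15-point difference kept. Power is for 6 × 25 = 150 workers per arm:

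δ = d / √{[p₁(1−p₁) + p₂(1−p₂)] × 1.24/150}

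Normal power is Φ(δ − 1.96). The t version uses a noncentral t with 12 − 2 = 10 df, because companies are randomised.

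| Rates | n per group | n × 1.24 | Power, normal | Power, t (10 df) |
|---|---|---|---|---|
| 10% vs 25% (plan) | 113 | 140 | 88% | 81% |
| 20% vs 35% | 151 | 188 | 75% | 67% |
| 30% vs 45% | 176 | 219 | 68% | 60% |
| 40% vs 55% | 186 | 231 | 66% | 57% |
| 50% vs 65% | 183 | 227 | 67% | 58% |
| 60% vs 75% | 165 | 205 | 71% | 62% |
| 70% vs 85% | 134 | 167 | 81% | 73% |
| 80% vs 95% | 88 | 110 | 95% | 90% |

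The plan row shows 88% rather than 80% because it uses 150 workers per arm instead of 140 and no continuity correction. Rows should be compared only within a column.

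**3. If new uptake is exactly as planned.** Suppose a share e of workers already use some measure, independently of new uptake (both are assumptions). The any-use rate is then e + (1 − e)·p, and the difference is (1 − e) × 15 points.

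- e = 20%: 0.20 + 0.80 × 0.10 = 28% vs 0.20 + 0.80 × 0.25 = 40%. The difference is 12 points; δ = 0.12/0.0604 = 1.99; power about 51%.
- e = 40%: 0.40 + 0.60 × 0.10 = 46% vs 0.40 + 0.60 × 0.25 = 55%. The difference is 9 points; δ = 0.09/0.0640 = 1.41; power about 29%.

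These are normal-approximation figures for follow-up proportions only, with no use of the baseline answer.

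**The case against.** The strongest reply is that existing use may be low. The Background says few workers use ergonomic measures in daily practice, and companies must have room to improve to be eligible. The item is also asked at baseline, and the planned mixed model tests change from baseline, so stable existing use is measured rather than ignored. A generic item suits the stated objective, since companies choose different measures. This stands in part. It weakens any claim about direction, and the calculations above give no credit for the baseline answer. It does not supply a two-month rate or make the 10% apply, and a worker who already answers yes cannot move from no to yes.

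Several stronger readings are tempting, but the document does not support them:

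- **The trial is sized for daily use.** Only the source of the 10% concerns daily use. The quantity sized is use of a new measure, with no frequency stated.
- **The outcome will sit near ceiling, or existing use will swamp the contrast.** No high existing rate is given. At a fixed 15-point difference, high base rates give more power, not less.
- **Use during the daily-practice test (step 5) will be counted as uptake.** This is possible, because testing precedes the decision to implement. But "The maximum duration of each guidance strategy is six months", and nothing dates step 5 to the last two months. A 10-working-day window at six months could overlap testing too.
- **Uptake of the chosen measure cannot be seen.** The additional item records it.

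**Conclusion.** The point holds as a mismatch between two stated definitions; it is not something left to an analysis plan. The 80% power and 140 per group do not apply to the primary outcome as defined.

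The size of the consequence depends on a rate that the protocol does not give. Over assumed base rates of 30–60%, like-for-like power falls from 88% to 66–71% (normal) or from 81% to 57–62% (t, 10 df). If planned uptake is diluted by 20–40% independent existing use, it is about 51–29% (normal). These results keep the plan's ICC of 0.01 and 25 workers per company. A reader might infer that the trial is underpowered. That is not established, since 80% vs 95% would give 95% and 90%.

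**What to change.** Make the powered quantity and the primary outcome the same variable.

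- **At minimum:** replace the 10%/25% inputs with an expected rate and difference for two-month any use, and restate the power as a range without enrolling more. The baseline questionnaire, pooled over both strategies, can supply the rate. This costs a short recalculation and a paragraph of text.
- **In addition:** name the 10-working-day item on the implemented measure as a secondary comparison between strategies, so that new uptake can be read separately from existing use. The data are already collected.
- **Making that item primary is an option, not a free correction.** It has no baseline value. It is not a daily-use measure either if scored as any use in 10 days, so the 10% would still need justification. It also depends more on whether the company implements anything, which strains an ICC of 0.01. With assumed ICCs of 0.05 and 0.20 the design effect is 1 + 24 × 0.05 = 2.2 and 1 + 24 × 0.20 = 5.8, and normal power for 10% vs 25% falls to about 65% and 30%. The change should be made only if the item's own rate and ICC are justified and the loss of the baseline is stated. It would also need a registry update.

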#### Secondary

##### Work ability

The measurement of work ability will be determined at baseline and after six months with the first three items of the Work Ability Index (wai)[21]: 1) current work ability compared with the lifetime best; 2) perceived work ability with respect to physical demands; and 3) perceived work ability with respect to mental demands.

##### Physical functioning

Physical functioning is assessed at baseline and after six months, and defined as limitations during 10 activities during a typical day, for instance climbing several flights of stairs or walking several hundred yards. Individual construction workers will be asked to state how much their health currently limits them in these 10 activities. The measurement will be determined with the subscale ‘physical functioning’ of the Dutch translation of the mos-36 questionnaire, the rand-36[22]. The categories for the answers are for each activity: ‘yes, serious limited’, ‘partly limited’, and ‘not limited at all’.

##### Limitations due to physical problems

Limitations due to physical problems are defined as whether individual construction workers had 1) spent less time on their work, 2) achieved less in their work, 3) were limited in and 4) had difficulty with their work or other regular daily activities as a result of their physical health. These four items will be measured with the subscale ‘limitations due to physical problems’ of the rand-36[22]. Each of the four statements must be answered with ‘yes’ or ‘no’.

#### Descriptive variables

The demographic characteristics, job characteristics and education will be assessed at baseline. The demographic characteristics are gender, and age (in years). The job characteristics are work experience in years as a construction worker, work experience in years in the current occupation, and whether the construction worker is in a managerial position. For education, the highest completed education level will be asked, divided into three categories: primary education, secondary (vocational) education or higher professional education. All descriptive variables will be assessed with self-formulated questions.

#### Process evaluation

The process evaluation of the two guidance strategies will be determined using indicators as defined by Linnan and Steckler [23] and Murta *et al*. [24]. The following process- and performance indicators will be evaluated: reach, dose delivered, dose received, precision, competence and satisfaction. An additional process indicator is the behavioural change of the construction workers.

Reach is defined as the attendance rate of the construction companies at the intervention. Attendance is defined as the number of construction companies participating in this study relative to the number of construction companies invited through the recruitment strategies. The attendance will be assessed by means of a logbook during the recruitment of the construction companies. Construction companies that will be contacted by the researcher (SV) and do not want to participate will be asked to explain why. Dose delivered refers to the amount or proportion of the intended intervention that is actually delivered to the participating contact persons of the construction companies. Within the six steps of the PE intervention, the dose delivered will be assessed by 31 performance indicators defined by van der Molen *et al*. [12]. Of these 31 performance indicators, 19 are defined as essential. The number of all performance indicators and of the 19 essential performance indicators delivered by the assignments of the ergonomics consultants to the steering committees will be assessed during the face-to-face guidance strategy by means of a logbook filled by an observer who is present at the meetings of the steering committee. For the e-guidance strategy, dose delivered will be assessed by means of the content of the emails from the ergonomics consultant to the contact person. Dose delivered is considered sufficient when at least all 19 essential performance indicators are delivered. When companies drop out of the study or do not follow the entire intervention, reasons why will be asked by the researcher (SV).

In addition, six performance indicators are defined for dose delivered of the steering committee to all construction workers within the included companies. The performance indicators are: 1) received information from the steering committee on the objective of the project, 2) received information on musculoskeletal complaints within the occupation, 3) received information on ergonomic measures, 4) involved with the choice of an ergonomic measure, 5) received information and training of the chosen ergonomic measure, and 6) tested the ergonomic measure in daily work. Dose delivered to the construction workers will be assessed by acquiring all information sent from the steering committee to the construction workers and via attendance lists during the meetings of the steering committee.

Dose received refers to the proportion of activities in the intervention that is actually performed by the steering committees of the construction companies. The performance indicators will be assessed by an observer by means of a logbook during the meetings of the steering committee during the face-to-face guidance strategy. For the e-guidance strategy, dose received will be assessed by means of a logbook by an observer who is present at the meetings of the steering committee and by means of the feedback of the assignments of the steering committees to the ergonomics consultant. Dose received is defined as sufficient when at least the 19 essential performance indicators are performed by the steering committee. Whether the dose is received by construction workers was assessed by seven questions about the seven performance indicators within the questionnaire after six months. In addition to the six performance indicators described above, an extra performance indicator is added to assess whether construction workers had read the delivered information. Dose received is sufficient when all seven performance indicators are received.

The precision of the intervention is defined as whether construction companies implement ergonomic measures described by the websites of Arbouw or codes of practice. If the implemented ergonomic measures are described by these websites or catalogues, the required precision is considered to have been reached.

The question of whether the ergonomics consultant has the competence to guide the steering committees of the construction companies will be asked with the help of a questionnaire after the six months of guidance has been completed. The contact person will be asked whether the assignments in preparation of the meetings were clear, whether the objectives of the four meetings were clear, whether the objectives of the feedback of the assignments to the ergonomics consultant were clear, whether the questions asked by the contact person were answered satisfactorily, and whether the ergonomics consultant was able to help with problems occurring during the six months of guidance. All items will be answered with yes or no and additional information on the given answer will be requested.

After six months, the company stakeholders within the steering committee are asked via a questionnaire whether they were satisfied with the guidance strategy and if it had been of value for the construction company. The questionnaire contains seven items, including the duration of the intervention, the duration of the meetings, the involvement of construction workers with the choice of an ergonomic measure. In addition, with two open-ended questions, members of the steering committee can give suggestions for improvements to the intervention, to the guidance strategy, and to the consultant. With the exception of the duration of the intervention and the open-ended questions, all items will be answered with yes or no. For all questions, additional information on the given answer will be requested.

The behavioural change of the construction workers consists of six topics: knowledge, attitude, motivation, ability to use, facilitation and culture. It is considered that the interventions will change the behaviour of construction workers towards working with ergonomic measures. Therefore, measurements of the items for behavioural change will be done at baseline and after six months by means of a self-made questionnaire.

First of all, the knowledge of the relationship between ergonomic measures, physical work demands and musculoskeletal disorders will be asked through two statements. An example of a statement is: “Due to long and frequent lifting and bending, I have an increased risk of low back pain. This can be reduced by using a raised hod”. The statements will be adapted for the different occupations, and construction workers will be asked if they agree with the statement. They can answer with a ‘yes’ , ‘no’ or ‘I don’t know’. Knowledge will be rated as good when both questions are answered affirmatively, and knowledge within a construction company is defined as good when the knowledge of 75% of all the construction workers within the company is rated as good.

The attitude of the construction workers towards working with ergonomic measures is asked with five yes or no items, such as “I only use ergonomic measures when I have physical complaints”, and is defined as good when four of the five items are scored positively. On the company level, attitude is considered good when at least 75% of the construction workers scored positively.

The motivation to work with ergonomic measures is asked through a single yes or no question. This question is: “When your employer provides ergonomic measures, are you willing to use them?” If the question is answered in the affirmative, construction workers are considered to have the motivation to work with ergonomic measures. Motivation is considered as good at company level when at least 75% of the construction workers answered the question in the affirmative.

Of the four earlier defined clusters of ergonomic measures, the ability to use these ergonomic measures will be asked. For each cluster, construction workers can assess their ability as good or poor.

As with the ability to use, the facilitation of each of four clusters of ergonomic measures will be assessed. In addition, a question is asked concerning whether the construction company has set up rules or procedures for the use of ergonomic measures.

The final topic of behavioural change is the culture of the construction company. By means of three items, the values and expectations of construction companies towards working with ergonomic measures will be asked. An example of such an item is: “It is expected of me and my colleagues that we work with ergonomic measures as much as possible”. The culture of the construction company is positive for an individual construction worker when all three items are answered affirmatively. At least 75% of the construction workers must experience a positive culture for the construction company to be considered as possessing a positive culture.

#### Economic evaluation

A cost-benefit analysis for each participating construction company will be made. At baseline, demographic characteristics of the employees with respect to sick leave will be assessed for the construction companies. The costs of the intervention will be assessed at the end of the intervention by multiplying the time spent by the ergonomics consultant with the hourly costs. In addition, at the end of the intervention, the director of the construction companies will be asked about the costs regarding employing the ergonomic measures and additional energy and the maintenance costs of the ergonomic measures. Furthermore, the director is asked if the production per working hour changed by using the ergonomic measure.

On the benefit side, construction workers will be asked at the end of the intervention how many days they could and did use the ergonomic measure during the previous 10 working days. In addition, construction workers are asked how they judge their physical work demands compared to working without the ergonomic measure. These three questions will provide a benefit for reducing risk factors for work-related musculoskeletal disorders. Another benefit aspect will be the change in production per working hour and change in quality of the work.

With the help of the Dutch Economic Institute of the Construction Sector, the above-mentioned aspects on the company level and on the individual worker level will result in a cost-benefit analysis for each construction company.

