Within the review of van Eerd *et al*. [16], fifteen out of 16 studies found that the presence of a PE specialist, defined as an ergonomics consultant, was a facilitator to the PE intervention process. The role of this ergonomics consultant was firstly to initiate and then to guide the PE intervention process [16]. In this study, we want to investigate the effect of two types of guidance strategies on the use of ergonomic measures, as well as on health outcomes. In addition, we want to evaluate the process and the costs-benefits of both guidance strategies. The two guidance strategies are: 1) a face-to-face guidance strategy in which the ergonomics consultant guides the PE intervention through face-to-face contacts with the PE team; and 2) an e-guidance strategy in which the ergonomics consultant guides the PE intervention by means of e-mail contacts with the PE team.

We hypothesise that the face-to-face guidance strategy will increase the use of ergonomic measures, work ability, and physical functioning while decreasing limitations due to physical problems more when compared to the e-guidance strategy. This would be due to a higher compliance to the face-to-face guidance strategy compared with the e-guidance strategy, as a result of the presence of the ergonomics consultant within the face-to-face guidance strategy. Although the financial costs will be higher in the face-to-face guidance strategy, due to more time spent by the ergonomics consultant during the guidance sessions, more financial benefits will be gained through reduced physical risk factors due to an increase in the use of ergonomic measures.

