### Study design

A randomised intervention trial with a follow-up at six months is performed to compare the effectiveness of the two ergonomic guidance strategies, a face-to-face guidance strategy and an e-guidance strategy, of a PE intervention. The effectiveness of both guidance strategies will be compared on the use of ergonomic measures, work ability, physical functioning, limitations due to physical problems of individual construction workers, a process evaluation and a cost-benefit evaluation.

According to the researchers, the study protocol did not met the criteria of the “Act medical-scientific research with human participants” and therefore, the Medical Ethics Committee of the Academic Medical Center Amsterdam (AMC) was not asked for approval of the study protocol.

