When construction companies are willing to participate, a meeting between the researcher (SV) and the companies CEO is established. During this meeting the construction companies will be informed about the purpose, the measurements, the two types of intervention and the randomized allocation to one of the intervention groups. Furthermore, they are informed that the costs of the ergonomics consultants will not be charged to the companies during the intervention. The only costs for the companies are the costs for renting or buying ergonomic measures. Construction companies agree to participate by signing an informed consent.

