The tenth email contact provides the agenda for the fourth meeting. Based on the test in daily work, a discussion will take place regarding whether the ergonomic measure will be implemented. In addition, points of interest will be defined for the further implementation. During the 11th email contact, an implementation strategy will be drawn up for the construction company based on three levels: measure, e.g. buying of hiring the measures; behaviour e.g. training of all construction workers; and organisation, e.g. deciding in which projects the ergonomic measure will be used (step 6).

After drawing up the implementation strategy, the process will be evaluated in email contact 12. Of each e-mail contact, the contact person will be asked whether the protocol is useful for the implementation of ergonomic measures. The 13th and final email contact contains the ending of the PE process.

After each meeting of the steering committee, all construction workers of the chosen occupations will be informed about the process of the intervention. In this manner, construction workers who are not part of the steering committee will be able to provide input throughout the entire intervention. The information obtained from each assignment given in each email contact will be returned by email to the ergonomics consultant. In each subsequent email contact of the ergonomics consultant, feedback will be given on the obtained information by the ergonomics consultant to the contact of the steering committee.

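### Intervention cost is set as consultant time only, so the company's own paid hours go uncounted and net benefit per company is overstated in both arms

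*Protocol article*

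**What the plan says.** The Economic evaluation section under Outcome measures sets the unit of analysis: "A cost-benefit analysis for each participating construction company will be made". It fixes the cost of guidance as the consultant's time, obtained "by multiplying the time spent by the ergonomics consultant with the hourly costs". It then asks the director for the "costs regarding employing the ergonomic measures and additional energy and the maintenance costs of the ergonomic measures". The benefit side takes in days of use, judged physical demands, quality of the work and the change in production per working hour.

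Under Recruitment of participants, companies are told: "The only costs for the companies are the costs for renting or buying ergonomic measures". The Background section expects that "the financial costs will be higher in the face-to-face guidance strategy, due to more time spent by the ergonomics consultant".

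The Interventions sections describe work done by company staff in both arms: setting up a committee, collecting information on work demands, arranging a supplier and a test environment, four committee meetings, worker instruction, and a test in daily work. For e-guidance the article adds: "The information obtained from each assignment given in each email contact will be returned by email to the ergonomics consultant". The Study design section lists the cost-benefit evaluation among the items on which the two strategies are compared.

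**The concern.** For a firm with fewer than 50 employees, taking several people off the job for four meetings, plus preparation and training, is a real cost of taking part. The plan counts labour when it produces a gain (production per working hour) but not when the intervention uses it up. A firm, or an occupational health service deciding whether to offer the programme, would read a net benefit from which one cost item is missing.

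The omission also bears on the comparison of strategies. The counted resource, consultant time, is the one the authors expect to be higher in the face-to-face arm. The uncounted resource, company time, may also differ between arms. A comparison based on the first alone is incomplete.

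**Working it through.** The article states no hours, hourly rate or cost total, so there is no figure to reproduce. The check sets the costing rule against the activities described and then sizes the gap under stated assumptions.

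**1. What is counted.** Let C be consultant hours and r the consultant's hourly cost. The plan's intervention cost is r × C. The costs of employing, powering and maintaining the measure are added separately.

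**2. What is used.** Let H be company hours spent on the guidance process and w the wage cost per hour. The full intervention cost is r × C + w × H. The rule therefore understates cost by w × H in each company. H is above zero in both arms because both require committee meetings and contact-person preparation. Other things equal, net benefit is overstated by the same w × H.

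**3. Size of H for meetings alone (assumed).** The Face-to-face guidance strategy section lists five stakeholder roles but lets one person fill several, so take 2 to 5 members. Take 1 to 2 hours per meeting, and the four meetings stated.
- Low: 2 × 4 × 1 = 8 hours per company.
- High: 5 × 4 × 2 = 40 hours per company.

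Preparation, and training or testing of workers outside the committee, come on top and are not sized here.

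**4. Effect on the comparison.** The difference in cost, e-guidance minus face-to-face, shifts by w × (H_e − H_f). The documented tasks are:
- *Common to both arms:* forming the committee, the overview of work demands, arranging supplier and test environment, four meetings, training and testing.
- *Extra in e-guidance:* 13 email contacts, written return of the assignments, and a first meeting explicitly held without the consultant.
- *Pulling the other way:* the Background section expects higher compliance in the face-to-face arm, so more of the planned meetings and assignments may actually take place there.

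If each email contact takes the contact person 0.25 to 2 hours (assumed), the e-guidance extra is 13 × 0.25 = 3.25 to 13 × 2 = 26 hours. Against that, one committee meeting not held in e-guidance removes 2 × 1 = 2 to 5 × 2 = 10 hours. With 3.25 extra email hours and one 10-hour meeting not held, H_e − H_f = 3.25 − 10 = −6.75 hours. With 26 extra hours and every meeting held, it is +26. The sign depends on quantities the article does not give.

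**The case against.** The strongest objection concerns direction. A reader might infer that e-guidance moves work from the consultant to the contact person, and that the costing rule therefore favours e-guidance and builds in the hypothesis that face-to-face costs more. The article does not support this. The face-to-face contact person has nearly the same preparation, both arms hold four meetings, and the consultant's absence is stated only for the first e-guidance meeting. Consultant time is measured in both arms and in e-guidance can include writing emails and giving feedback, so the cost hypothesis can still be refuted by the data. This objection stands.

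Two further inferences also fail. Staff time cannot be called the company's main outlay, because the measures may include cranes and other costly equipment and nothing ranks the two. Nor can a ratio of company meeting hours to consultant meeting hours serve as evidence, because it only returns the committee size one assumed.

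It can also be said that the costs of employing the measure might cover paid training time, that an article need not itemise costs, and that the recruitment statement describes what companies are charged. Some training time might indeed be reported under that item. Committee meetings and preparation would hardly be, because they come before the decision whether to implement. The article is also not silent here: it states a formula for intervention cost, and that formula contains consultant time only. Nor is the analysis limited to what companies pay during the trial, since it counts consultant time that the research budget covers.

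Finally, the economic evaluation is descriptive and is neither a primary nor a secondary outcome. That limits the weight of the point, but a missing cost item distorts a descriptive balance as well.

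**Conclusion.** The point holds for the level of cost in both arms. As written, the rule leaves out the company's own paid hours, so cost per company is understated and net benefit overstated. The sign follows from the definition. The size, about 8 to 40 meeting hours per company, rests entirely on assumed committee size and meeting length, and no money value can be given because the article states no wage rate.

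For the comparison of strategies the conclusion is conditional: it is biased if company hours differ between the arms. The email work makes a tilt towards e-guidance plausible, but the expected difference in compliance could offset or reverse it. An unsettled direction is itself a reason to measure the hours. The primary and secondary effect analyses are not affected.

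**What to change.** Add company labour to the intervention cost in both arms:

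- Have the observer, who is already planned to attend committee meetings in both arms, record the duration of each meeting and who attended. The article does not say that the logbooks or attendance lists record duration, so this is a new field.
- At the end, ask the contact person once for hours spent on preparation, email work and worker training.
- Value these hours at a stated wage rate, and take care not to count again any training time the director reports under the costs of employing the measure.
- Report strategy cost and net benefit per company with and without company labour. The planned result is then kept and the effect of the added item is visible.

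The price is one logbook field, one question, a wage rate and some recall error in the contact person's answer.
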